***Mailing procedure***

An illustrated summary of the mailing procedure is provided in Figure 2. All eligible patients will be sent a study pack as outlined above. Those who do not respond within 2 weeks will be contacted again with a postcard reminder. At 4 weeks those who have not responded will be sent a second study pack and reminder letter. At baseline, patients who have still not responded at 8 weeks will be recorded as non-responders and will not be contacted again at any point in the study and their medical records will not be accessed. Participants who respond to the questionnaire but who do not consent to further contact, which will be specified on the consent form as being in 3, 6 and 12 months time, will also be recorded in the database as a non-consenting responder, ensuring that we do not contact them again in the future (this may occur by returning a completed or blank questionnaire or verbally by telephone conversation).

*Follow-up*

Participants who return a questionnaire and consent to participate at baseline will be sent a follow-up questionnaire at 3, 6 and 12 months following their index consultation. In order to maximise participation a short questionnaire, including only minimal data collection items (outlined below), will be sent to participants who have not responded to the full postal questionnaire at 6 weeks. At 6 and 12 month follow-up points an additional telephone call will be used at 8 weeks (for those participants who provided a telephone number in their baseline questionnaire) to attempt to contact non-responders in order to get information on their pain intensity at that time. Three telephone call attempts will be made to contact each participant. The mailing procedure is outline in Figure 2.

**Figure 2:** Mailing procedure

[figure not shown]

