|  | Anxiety | Nervousness and worrying in the past month | Modified GAD-2 (26) | 2 |
| **Control Arm** | Pain intensity | Current pain intensity (of the index pain, at the time of the index consultation) | 0-10 NRS (48) | 1 |
| NRS – numerical rating scale | | | | |

*2a. Full postal Questionnaire*

The postal questionnaires are designed to collect information on descriptive characteristics of the participants, in-depth depression and anxiety measures, pain-related characteristics and detailed data collection of our outcome measures. The items to be included in each of the four postal questionnaires (baseline, 3, 6 and 12 months) are summarised in Table 2. Further details of the outcome measures of interest are provided below.

*Outcome measures*

1. *Primary outcomes*

The primary outcome measure of the study will be index pain severity across the study time period. The Chronic Pain Grade [48] will be included in each of the postal questionnaires, this includes the question “How would you rate your pain on a 0-10 scale at the **present time** where 0 is “no pain” and 10 is “pain as bad as it could be”?”. This question is also part of the consultation screening template for both arms of the study.

1. *Secondary outcomes*

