Costs: Health sector costs will include primary and secondary care contacts, investigations, medication and contacts with other health care professionals such as physiotherapists and community psychiatric nurses. Primary health care resource use (GP and practice nurse consultations/home visits) and medications will be collected from a review of primary care medical records, covering the full 12 month follow-up period for all study participants. Information on secondary care attendances and patient borne costs will be gathered using the postal self-report questionnaires. Questions on patients’ personal expenditure will concentrate on private health care use and over-the-counter treatments. Productivity costs will be calculated using data collected on occupation and days off work due to illness. Unit costs will be obtained from standard sources and health care providers. Due to the nature of the study, generic health care resource use will be collected (i.e. not specific to the treatment of OA). Information on resource use from the self-report questionnaires will be collected at 6 months and 12 months, with each questionnaire covering a 6 month recall period.

Quality of life measures: All patients will be asked to complete the 5-level version of the EuroQoL-5D (EQ-5D) [55] questionnaire at baseline, 3 months, 6 month and 12 months in order that quality-adjusted life years (QALYs) over the 12 month time period can be calculated for each study participant. The QALYs combine information on health-related quality of life and survival. The SF-12 will also be included as a measure of generic health-related quality of life, thus allowing an alternative method of calculating QALYs using the SF-6D in a sensitivity analysis.

The conceptual domains, operational definitions and empirical measures of each of the items included in the postal questionnaires are detailed in Table 2. This table also highlights in which of the questionnaires (baseline, 3, 6 or 12 months) the item is included.

**Table 2:** Summary of full postal questionnaire content

| **Conceptual domain** | **Operational definition** | **Empirical measure** | **Number of items** | **Time** |
| --- | --- | --- | --- | --- |
| **Primary Outcomes** |  |  |  |  |
| Pain intensity | Current intensity of the index pain | NRS 0-10 * | 1 | B, 3FU, 6FU, 12FU |
| **Secondary Outcomes** | |  |  |  |

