| Disability | Composite characteristic pain interference with daily activities, recreation and work during the past 3 months. | Number of days (1 item) and NRS 0-10 (3 items provide composite disability score of 0-100)* | 4 | B, 3FU, 6FU, 12FU |
| Characteristic pain intensity | Composite current and past and average pain intensity during the past 3 months. | NRS 0-10 (3 items provide a composite characteristic pain intensity score of 0-100)* | 3 | B, 3FU, 6FU, 12FU |
| Index pain location | Site of index pain complaint | Choice of anatomical site | 1 | B |
| Nature of onset | Traumatic onset | Yes / no / unsure | 1 | B |
| Episode duration | Time since last whole month free from this pain | Episode duration (56) | 1 | B, 3FU. 6FU, 12FU |
| Days in pain | Days in past 6 months with index pain | No days / 1-30 days / 31-89 days / 90+ days | 1 | B, 6FU, 12FU |
| Multiple site / chronic widespread pain | Pain in sites other than the index site over the last month. Manchester definition of widespread pain; Keele definition of number of pain sites; chronicity of pain; pain in the knee or hip | Yes/no; Body manikin (57,58) | 4 | B, 3FU, 6FU, 12FU |
| Pain consultation | First consultation for this pain complaint | Yes / no | 1 | B |
| Pain improvement | Improvement in pain at index pain site | 6 point Likert scale | 1 | 3FU, 6FU, 12FU |
| Further pain consultation | Consulted since index consultation with the same pain site | Yes / no | 1 | 3FU, 6FU, 12FU |
| Satisfaction with consultation | Satisfaction with questions asked during consultation | Yes/no/unsure; details; list of items asked | 4 | B |
| Physical function related to knee and/or hip pain | Degree of difficulty with 8 daily activities | Short form WOMAC function subscale (50) | 8 | B, 3FU, 6FU, 12FU |
| Catastrophic coping | Catastrophic coping relating to index pain | Pain catastrophising scale (54) | 9 | B |
| Anxiety | Generalised anxiety symptoms in past 2 weeks | GAD-7 (53) | 7 | B, 3FU, 6FU, 12FU |
| Depression | Depressive symptoms in past 2 weeks | PHQ-8 (59) | 8 | B, 3FU, 6FU 12FU |
| Discussion of mood in consultation | Did doctor ask about mood during index consultation | Yes / no / unsure | 1 | B |
| Diagnosis of depression | Ever diagnosed by doctor as depressed | Yes / no / unsure | 1 | B |
| Diagnosis of anxiety | Ever diagnosed by doctor with an anxiety disorder | Yes / no / unsure | 1 | B |
| **Quality of life measures** | |  |  |  |

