| General health | Mental and physical well-being | SF-12 (49) | 12 | B, 3FU, 6FU 12FU |
| General health | Utility-based quality of life | EuroQol-5D (55) | 5 | B, 3FU, 6FU 12FU |
| Comorbidities | Ever been diagnosed with any from a list of possible comorbidities | Yes |  | B |
| Fractures | Ever fractured hip/wrist/other bones |  |  | B |
| Falls | Falls in the past 12 months | Yes/No | 1 | B |
| **Healthcare costs** |  |  |  |  |
| Medication usage | Select from list of analgesic and psychiatric medicines that currently taking |  |  | B |
| Health care resource use | Use of non-primary care health care resources | Yes/No and details of resource use if Yes | 3 | B, 6FU, 12FU |
| OTC medication | OTC medication expenditure | Details of OTC medications |  | 6FU, 12FU |
| **Miscellaneous** |  |  |  |  |
| Age | Age at index consultation | Date of birth | 1 | B, 3FU, 6FU, 12FU |
| Sex | Sex | Male / Female | 1 | B, 3FU, 6FU, 12FU |
| Employment status and absence from work | Employment status at time of questionnaire and days of work absence | Yes/No and details | 10 | B, 6FU, 12FU |
| Socioeconomic status | Occupational class based on individual (i) current or (ii) most recent job title | Job title – categorised as manual / non-manual (60,61) | 2 | B |
| Living arrangement | Live alone | Yes / No | 1 | B |
| Marital status | Marital status at time of Baseline Questionnaire | Married / Single / Divorced / Widowed / Separated / Cohabiting | 1 | B |
| Social support | Availability of instrumental and emotional support (yes/no/no need) | Single items (62) | 2 | B, 6 FU, 12 FU |
| Obesity | Body Mass Index | Height (m / ft, in), weight (kg / st, lb) | 2 | B |
| B – baseline; FU – follow-up (in months); OTC – over the counter; NRS – numerical rating scale; * 7 items form the Chronic Pain Grade (48). | | | | |

*2b. Short postal questionnaire*

This questionnaire will contain a minimum set of data that we are interested in, namely: Chronic Pain Grade and EQ-5D (summarised in Table 3).

**Table 3:** Summary of short postal questionnaire content

| **Conceptual domain** | **Operational definition** | **Empirical measure** | **Number of items** | **Time** |
| --- | --- | --- | --- | --- |
| Index global severity | Composite characteristic pain intensity, interference with activities, and disability days (of the index pain, in the month preceding index consultation) | Chronic Pain Grade (48)* | 7 | 3FU, 6FU, 12FU |

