| General health | Utility-based quality of life | EuroQol-5D (55) | 5 | 3FU, 6FU 12FU |
| Age | Age at index consultation | Date of birth | 1 | 3FU, 6FU, 12FU |
| Sex | Sex | Male / Female | 1 | 3FU, 6FU, 12FU |
| FU – follow-up (in months); * Chronic pain grade includes primary outcome measure of current pain intensity | | | | |

*2c. Telephone questionnaire*

At each of the 6 and 12 month follow-up timepoints we will attempt to contact by telephone participants who do not respond to either the full or short questionnaires. Participants will be asked the brief questions regarding the intensity of the pain in their index pain site and how much this interferes with their daily activities. They will be asked to rate these on a numerical rating scale of 0-10 (summarised in Table 4).

**Table 4:** Summary of telephone questionnaire content

| **Conceptual domain** | **Operational definition** | **Empirical measure** | **Number of items** | **Time** |
| --- | --- | --- | --- | --- |
| Pain intensity and interference | Pain intensity and interference with activities | NRS (0-10) | 2 | 6FU, 12FU |
| Age | Age at index consultation | Date of birth | 1 | 6FU, 12FU |
| FU – follow-up (in months); NRS – numerical rating scale | | | | |

1. *Medical record review*

A medical record review will take place for all participants who have given their consent (at the time of the baseline questionnaire) to have their medical records reviewed (summarised in Table 5). This will allow us to download their data from the consultation screening template. Date of consultation, general practice and index Read code information will also be collected at this time. After the 12 month follow-up period a more detailed review will be carried out to enable us to assess prescriptions, referrals for further treatment, and number of consultations and whether these are for OA or mood problems. It will also allow us to determine whether there had been any previous diagnosis or treatment for depressive or anxiety symptoms. This data will provide primary health care resource use for the health economic analysis. The information collected on the treatment paths taken for patients who have a completed template will be fed back to practices following the 12 month record review, allowing practices in the intervention arm to see how closely they have followed recommended NICE guidelines. This information will also be of interest to GP practices in the control arm.

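### Table 3 gives the short follow-up questionnaire's Chronic Pain Grade a recall window that lies before the intervention and contradicts Table 2

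*Protocol*

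**What the plan says.** Under Data collection, the Protocol says that the Chronic Pain Grade "will be included in each of the postal questionnaires". Two tables then define what it measures.

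- **Table 2 (full questionnaire).** The disability row reads "Composite characteristic pain interference with daily activities, recreation and work during the past 3 months" and the characteristic pain intensity row reads "Composite current and past and average pain intensity during the past 3 months". Both are collected at baseline, 3, 6 and 12 months and are listed as secondary outcomes. The primary outcome has its own row, "Current intensity of the index pain", with no recall period.
- **Table 3 (short questionnaire).** The operational definition is "Composite characteristic pain intensity, interference with activities, and disability days (of the index pain, in the month preceding index consultation". The same row gives the instrument, item count and schedule as "Chronic Pain Grade (48)* | 7 | 3FU, 6FU, 12FU", so there is no baseline use. A footnote adds: "Chronic pain grade includes primary outcome measure of current pain intensity".

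Mailing procedure says who receives the short form: it "will be sent to participants who have not responded to the full postal questionnaire at 6 weeks". Follow-up is timed from the index consultation, and Activation of the screening template places the intervention inside that consultation.

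**The concern.** The two tables describe the same seven-item instrument at the same follow-up visits but disagree on two features of the window: its length (one month against three) and its anchor (the index consultation against the date of the questionnaire). The anchor is the serious one. A period that ends when the patient walks into the index consultation cannot reflect anything the template or the GP's later care has done.

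If the short form asks what Table 3 says, one outcome variable would hold post-intervention data from full-form responders and pre-intervention recall from short-form responders. Which window a patient is measured on would depend on how readily they reply. At stake are the secondary composites that the Protocol plans to derive from this instrument: characteristic pain intensity, the disability score and the count of disability days. Pain interference also appears in the hypothesis under Primary objective, although Data collection classes it as secondary.

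**Working it through.** **1. The plan's own figure.** Sample size uses M = 2(z_α + z_β)²{1 + (n−1)ρ}/(nΔ²) with n = 3, ρ = 0.5, Δ = 0.2, α = 0.05 (two-sided) and β = 0.10.

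- M = 2 × (1.960 + 1.282)² × 2 / (3 × 0.04) ≈ 350 per arm, as stated.
- Design effect: 1 + 29 × 0.03 = 1.87, and 2 × 350 × 1.87 = 1309, as stated.
- Non-response: 1309 / 0.75 ≈ 1745, as stated.

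This calculation is for the pain response, whose primary measure is the present-time item. That item has no recall window, so correcting Table 3 changes none of these figures.

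**2. Where each window falls.** Take the short form as sent 6 weeks (about 1.4 months) after the full questionnaire for that visit. Times are months after the index consultation.

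| Visit | Short form sent | Table 3 window | Past 3 months, at short-form date |
| --- | --- | --- | --- |
| 3 months | about 4.4 | −1 to 0 | about 1.4 to 4.4 |
| 6 months | about 7.4 | −1 to 0 | about 4.4 to 7.4 |
| 12 months | about 13.4 | −1 to 0 | about 10.4 to 13.4 |

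The Table 3 window is the same pre-intervention month at all three visits, so the recalled items would also show no change over time. The Table 2 window lies wholly after the index consultation at each follow-up. For a full form completed at exactly 3 months it runs from 0 to 3.

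**3. Which items are exposed.**

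- Disability score: three 0-10 items, all recalled. All exposed.
- Disability days: one recalled item. Exposed, and also on a different scale, because a one-month count cannot exceed 31 days.
- Characteristic pain intensity: three items, one of which is current pain. Two of three exposed.
- Present-time pain (primary outcome): asked as of now. Not exposed.
- EQ-5D: a separate row of Table 3. Not exposed.

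**4. Illustrative dilution.** Let s be the share of follow-up composites that come from the short form. The Protocol does not give s, so 10-25% is assumed. It also gives no effect size for the composites, so the 0.20 SD planning effect for pain is borrowed. Further assumptions are that recalled pre-index items show no difference between arms, that the items contribute equally, and that the composite SD is unchanged.

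- Disability score: 0.20 × (1 − s). For s = 0.10 this is 0.18 SD; for s = 0.25 it is 0.15 SD.
- Characteristic pain intensity: 0.20 × (1 − 2s/3). For s = 0.10 this is 0.20 × 0.933 ≈ 0.187 SD; for s = 0.25 it is 0.20 × 0.833 ≈ 0.167 SD.

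**The case against.** The best defence is that Table 3 is only a summary and may simply be worded wrongly. The printed short questionnaire is not in the Protocol. Elsewhere the text treats the short form as the ordinary Chronic Pain Grade: the same instrument goes into every postal questionnaire, Data collection refers the reader to Table 2 for item definitions, and the short form is described as a minimum data set with no hint of a modified version. This stands. A reader might infer from Table 3 that short-form responders actually report pre-intervention pain, but the document does not show that. It shows a definition that would produce that result if followed.

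Three other stronger readings also fail:

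- **That the primary outcome is compromised.** The present-time item is in the short form by the Table 3 footnote, and a recall window cannot govern a question about pain now.
- **That the mixture of windows biases the comparison between arms in one direction.** Minimising systematic bias says both arms receive identical questionnaires, and Mailing procedure describes one process for all participants. Nothing suggests that short-form use differs by arm.
- **That every composite is diluted by the full factor 1 − s.** This ignores the current-pain item within characteristic pain intensity.

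The defence does not remove the contradiction. The cell sits under the operational-definition column, its row applies only to follow-up, and anyone building or analysing the short form could reasonably follow it. Nor could a later analysis plan recover answers collected over the wrong period.

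**Conclusion.** The point holds as an error in a stated outcome definition. Table 3's window is unusable for a follow-up instrument and conflicts with Table 2 on both length and anchor. The consequence is conditional: if the printed short form follows Table 3, its recalled items measure a pre-intervention month and cannot be pooled with full-form data. If the printed form follows Table 2, only the Protocol text is wrong.

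The reach is limited to the recalled items of the secondary Chronic Pain Grade composites; the primary analysis does not depend on them. The dilution figures (0.18-0.15 SD for disability, about 0.187-0.167 SD for characteristic pain intensity) are illustrations resting on an assumed short-form share and a borrowed effect size, not estimates of what happened. The point should be corrected, but it does not threaten the trial's main conclusion.

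**What to change.** 1. Change the Table 3 operational definition to the Table 2 window, the past 3 months at each follow-up.
2. Check the printed short questionnaire against the corrected definition.
3. Only if that form is found to have used the pre-index window, correct it for later mailings, leave the recalled items of forms already returned out of the composite scores, and keep their present-time item. If the form already used the Table 2 window, no data need be set aside.

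The cost is one table cell and a wording check. The Timeline in the amendment shows 8 practices in block 1 closing and 5 in block 2 active, 13 of about 44, with recruitment expected to run to about November 2012. Most follow-up mailings were therefore still to come when this text was written.

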***Study administration and data storage***

The Study Coordinator will oversee the day to day running of the study. Members of the PCRN will download details of patients who have a completed template (name, address, date of birth and EMIS identification code) on a weekly basis from each practice. Two secure databases will be designed specifically for use in this study. One will be a mailing database where all details downloaded from practice databases will be stored. A unique study number will be applied to each potential participant. The Research Support Coordinator will arrange mailings of the study pack, following the mailing procedure outlined above. On return of a completed questionnaire details will be entered into the mailing database to ensure no unnecessary reminders are sent to participants. Details of informed consent will be stored on the mailing database. Following the reminder period of the mailing procedure, eligible patients who do not respond to the baseline questionnaire will be recorded as non-responders in the mailing database and will not be contacted again at any stage of the study.

The second database will be used to store all data collected during the study. In this database participants will only be identified by study number. Data will be entered into both databases by trained members of the administration team who will be blinded to cluster allocation. Access to the databases will be restricted to those members of the team that are working on this study. The coding schedule for the study questionnaires will be used to inform database design and to facilitate data entry. The data entry of a randomly selected 1 in 10 questionnaires will be checked by a member of the administration team who has not been inputting data from this study and who is blinded to cluster allocation. Details of data entry accuracy will be kept by the Research Support Coordinator and the study statistician and reported to Trial Steering Committee and Date Monitoring Committee. For those participants who agree to a medical record review, data from their completed screening template will be downloaded.

Throughout the entire mailing process, fortnightly checks will be carried out at each practice, by a member of the PCRN, to determine any patient deaths and departures. This will ensure we do not inappropriately contact any patients throughout the time period of the study. The name and address details of non-respondents will be erased after a reasonable amount of time. The NHS tracing system will be used to search for any non-responders to ensure we have the correct postal address.

On receipt of a completed questionnaire it will be checked for missing questions or an incomplete consent form, if it seems that any pages have been skipped over by accident then these pages will be photocopied and sent, along with an accompanying letter and stamped addressed envelope, to the participant for completion. If answers in the questionnaire are missing or appear to be ambiguous they will be coded as such in the database.

Regular meetings will be held with the Research Support Coordinator, PCRN and Study Coordinator to resolve any arising issues with regard to the everyday running of the study. Requests for data must be made in writing along with a detailed analysis plan to the data custodian for the study. Questionnaires and study consent sheets will be stored securely in separate locations to ensure participant confidentiality.

The trial will be conducted in compliance with this protocol and Good Clinical Practice guidelines. The Trial Steering Committee and Data Monitoring Committee will monitor the progress of the trial and, following their terms of reference, will intervene where they deem necessary.

